**Methods:**

This mixed methods study used a previously completed qualitative phase (n=6) to inform the development of a web-based platform and intervention called SmartManage. The pilot phase study (n=50) involved randomization (1:1) into either 10 sessions of adapted CBSM or an attention control health promotion. Both conditions used the SmartManage platform, a web-based eHealth program designed to deliver CBSM and health promotion content and host *live* groups. Feasibility and acceptability (eg, rates of participant engagement and retention) were the primary outcomes.

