**Content related to health and health care**
“In general, how much did you like the information presented on the website?”“Were the topics we included relevant to your experience as an HIV+ cancer survivor?”“What specifically did you learn that you can use to improve your health and well-being?”“What problems or challenges do you have that were not addressed appropriately or to your satisfaction?”“What else would you like to see included on the site?”

All study procedures involving participants are intended to be completed remotely via secure Health Insurance Portability and Accountability Act–compliant video conferencing software. This includes the documentation of informed consent and administration of assessments, both of which will be captured using the secure REDCap (Research Electronic Data Capture; Vanderbilt University) platform.

The pilot study will enroll 50 SMM who are HIV positive with a history of a nonmetastatic solid tumor or blood cancer, who will be randomly assigned (1:1) to receive either 10 individual sessions of video-adapted health promotion (HP) content (educational control) or 10 group-based sessions of the SmartManage intervention facilitated by trained interventionists (Figure 1). Before randomization, participants will complete a self-report assessment battery (baseline or T1; Table 1), which they will complete again immediately after treatment (T2). Participants will be compensated US $20 for completing the T1 questionnaire, US $10 for each of the 10 intervention or control sessions, and US $30 for the T2 questionnaire, yielding a maximum of US $150 compensation for completing the study procedures.

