#### Aim 2: Randomized Controlled Pilot Testing of Intervention (Feasibility, Acceptability, and Intended Effects)

For phase 2, descriptive statistics will be used to characterize the sample and inspect data quality. We will examine the amount, pattern, and randomness of missing data to determine appropriate statistical methods to handle missingness. Type 1 error will be set to 5% (α=.05) for calculating CIs and performing hypothesis testing. The α values will be adjusted for multiple comparisons, as needed.

We will examine feasibility via engagement and retention rates as well as cost indicators. Intervention acceptability will be evaluated using continuous data from the exit survey (USE questionnaire). These analyses will be primarily descriptive; however, we will use general linear modeling (eg, independent samples 2-tailed *t* test and ANOVA) to determine whether there are significant differences in feasibility and acceptability by sociodemographic, medical, and psychosocial variables. We will examine the distributions to determine whether alterations to the data analytic plan are needed, for example, using nonparametric methods. If >10% of the data are missing completely at random, we will use multiple imputation techniques.

To evaluate the intended effects of the intervention, we will analyze continuous scores on measures of stress, disease-related distress, and HRQoL. We will use paired samples *t* tests to examine whether these variables improve significantly within groups from pre- to postintervention measurement. We will use repeated measures ANOVA to determine whether these potential changes remain significant, accounting for the sociodemographic, medical, and psychosocial covariates described earlier. We will also use independent samples *t* tests to analyze potential differences in outcomes between the study groups (SmartManage intervention vs educational control). These will be analyzed using repeated measures ANOVA to explore whether effects remain when accounting for sociodemographic, medical, and psychosocial covariates.

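### The secondary between-arm comparison does not name the T1 score of the same scale as a covariate; ANCOVA would use data already collected and be more precise than either planned analysis

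*Protocol article*

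**What the plan says.** All references are to the protocol article.

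- **Data collected.** The Study Design section states: "Before randomization, participants will complete a self-report assessment battery (baseline or T1; Table 1), which they will complete again immediately after treatment (T2". Each participant therefore has a pre-randomization value on each outcome scale.
- **Outcomes.** In the Data Analytic Plan, Aim 2: "we will analyze continuous scores on measures of stress, disease-related distress, and HRQoL".
- **Arm comparison, first step.** The same section names independent-samples t "tests to analyze potential differences in outcomes between the study groups (SmartManage intervention vs educational control". It does not define whether the compared quantity is the T2 score or the change from T1.
- **Arm comparison, second step.** "These will be analyzed using repeated measures ANOVA to explore whether effects remain when accounting for sociodemographic, medical, and psychosocial covariates". The T1 score of the scale under analysis is not named among these covariates.
- **Size and error rate.** "The pilot study will enroll 50 SMM who are HIV positive", and in the Abstract, "The pilot phase study (n=50) involved randomization (1:1", so 25 per arm. "Type 1 error will be set to 5% (α=.05) for calculating CIs and performing hypothesis testing".
- **Status.** The section on intended effects says that efficacy testing is not the study's purpose. Feasibility and acceptability are the primary outcomes.

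**The concern.** In a randomized comparison of a scale measured before and after treatment, the baseline value of that scale is usually the most prognostic covariate available. Here the plan spends degrees of freedom on three classes of other covariates and does not name that one.

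What is at stake is precision and how chance imbalance is handled in a small trial. A T2-only t test carries any baseline difference between arms into the estimate, in proportion to r. A change score over-corrects it whenever r is below 1. ANCOVA removes it in expectation.

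Because the outcome of the t test is undefined, the text also permits two analyses that can give different estimates from the same data. The comparison with the control condition is the stated secondary aim, so its estimates and intervals will be read.

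**Working it through.** **Inputs from the article.** N = 50, allocated 1:1, so 25 per arm; α = 0.05; two occasions, T1 and T2. The retention target of 85% gives 0.85 × 50 = 42.5, so about 21 completers per arm. The article gives no SD, effect size, power or correlation, so there is no stated figure to reproduce.

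**Assumptions.** Equal SD at T1 and T2; T1-T2 correlation r from 0.3 to 0.7; independent observations; two-sided tests. The article writes "independent samples 2-tailed" only for the feasibility and acceptability t tests, so two-sidedness is assumed for the intended effects.

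**Step 1. Variance of the arm difference, relative to a T2-only t test.**
- T2-only t test: 1.
- Change-score t test, or group-by-time term with two occasions: 2(1−r). A simulated data set with 25 per arm confirmed the equivalence: the group-by-time F and the squared change-score t were both 5.4026.
- ANCOVA on T1: 1−r², multiplied by 1 + 1/(N−4) for estimating the slope. The penalty is 1/46 = 2.2% at N = 50 and 1/38 = 2.6% at N = 42.

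**Step 2. What ANCOVA removes, before the penalty.** Against T2-only: 1 − (1−r²) = r². Against change: 1 − (1−r²)/[2(1−r)] = 1 − (1+r)/2 = (1−r)/2.

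| r | Change vs T2-only variance | ANCOVA vs T2-only variance | Removed vs T2-only | Removed vs change |
|---|---|---|---|---|
| 0.3 | 1.40 | 0.91 | 9% | 35% |
| 0.5 | 1.00 | 0.75 | 25% | 25% |
| 0.6 | 0.80 | 0.64 | 36% | 20% |
| 0.7 | 0.60 | 0.51 | 49% | 15% |

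Below r = 0.5 the change-score analysis is less precise than leaving the baseline out.

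**Step 3. Does the penalty reverse the ranking?** At N = 42, ANCOVA beats T2-only when (1−r²)(39/38) < 1, that is r² > 1/39, or r above about 0.16. It beats the change score when (1+r)(39/38) < 2, or r below about 0.95. The ranking holds over the whole assumed range.

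**Step 4. Difference detectable with 80% power, 21 per arm.** This uses the noncentral t distribution with noncentrality d/[s√(2/21)], where s² is the relative variance from Step 1 (with the penalty for ANCOVA). The degrees of freedom are 40 for the t tests and 39 for ANCOVA.

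| r | T2-only | Change | ANCOVA |
|---|---|---|---|
| 0.5 | 0.89 SD | 0.89 SD | 0.78 SD |
| 0.6 | 0.89 SD | 0.79 SD | 0.72 SD |
| 0.7 | 0.89 SD | 0.69 SD | 0.64 SD |

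**Step 5. Imbalance.** With 25 per arm, the chance baseline difference has standard error √(2/25) = 0.28 SD. A gap of at least one standard error arises in roughly one trial in three. At r = 0.6, a gap of 0.28 SD shifts a T2-only estimate by 0.6 × 0.28 = 0.17 SD. It shifts a change-score estimate by (1−0.6) × 0.28 = 0.11 SD in the opposite direction.

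**The case against.** The strongest reply is that the plan does use the baseline. The sentence after the t test puts the same comparison through repeated measures ANOVA, and the only repeated occasions are T1 and T2. The t test may itself be on change scores. Both methods are valid under randomization, the comparison is secondary, no sample size rests on it, and a journal article condenses its model specification.

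Much of this stands. A reader might infer that the plan ignores the baseline score. That describes only the t test, and only if it is read as a T2 comparison. A reader might also infer that a third or more of the precision is lost. The article gives no correlation to support that. Against a T2-only test, a one-third saving needs r ≥ √(1/3) = 0.577 on the variance scale, or r ≥ √(1 − (2/3)²) = 0.745 on the standard-error scale. At r = 0.577, the saving against the planned ANOVA is only (1 − 0.577)/2 = 21%. Finally, the Discussion says that lessons from the study may inform larger trials; it does not say that the effect estimates will.

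What does not stand is that the ANOVA settles the matter. It is less efficient than ANCOVA across the assumed range, and the text does not say that its group-by-time term is the treatment effect. Nor is this only a detail left to a fuller document: the article itself names both methods.

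**Conclusion.** The point holds as one of efficiency and clarity in a secondary analysis. Neither planned between-arm analysis names the T1 score of the same scale as a covariate, and the outcome of the t test is not defined. ANCOVA would remove 9% to 49% of the variance of a T2-only t test, or 35% to 15% of the variance of the change-score or group-by-time analysis, as r runs from 0.3 to 0.7, less about 2%. These sizes rest on assumed correlations and equal SDs, and the article cannot narrow them. The planned tests are not invalid, and the primary feasibility and acceptability outcomes are untouched. Severity is modest; the change is worth making because it is nearly free.

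**What to change.** For each continuous scale in the intended-effects analysis, fit a linear model of the T2 score on arm with the T1 score of that scale as covariate. Report the adjusted difference between arms with its 95% CI. Use this in place of the independent-samples t test and the group-by-time ANOVA. Doing so also removes the doubt over whether T2 or change scores are compared. Any further covariates can be added to the same model as a sensitivity analysis.

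The cost is a change of wording in the Data Analytic Plan and one degree of freedom per model. No new data are needed.

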### SmartManage for HIV and Cancer Survivors: Adapted CBSM for Lesbian, Gay, Bisexual, Transgender, and Questioning Individuals Dually Diagnosed With HIV and Cancer

The SmartManage CBSM intervention was adapted from the manualized CBSM intervention [17], with an additional focus on psychosocial issues relevant to SMM, as well as focus on comanaging HIV and cancer. The adapted CBSM SmartManage for HIV and cancer intervention incorporates cognitive behavioral therapy techniques to facilitate changes in domains known to impact symptom burden, HRQoL, physical functioning, and self-management (see Table 2 for the session outline). The CBSM intervention using the SmartManage platform seeks to promote coping and resilience through the use of practical tools (relaxation training, increasing physical activity, and social support), general and diagnosis-specific information, and cognitive behavioral therapy–based strategies (eg, cognitive restructuring), with added focus on the role of sexual minority stress and issues relevant to SMM (see Figure 2 for conceptual model). Throughout the 10 sessions that lasted for 90 minutes, participants are taught to recognize the antecedents of negative mood and systematically evaluate cognitive distortions to improve symptom management, interpersonal adjustment, and HRQoL. Intervention groups consist of 4 to 6 participants led by a trained therapist (master’s level or psychology doctoral students) with experience in working with sexual minority clients. Participants are encouraged to share relevant experiences and to practice skills during the session. For example, a participant who expresses anger that a friend did not call him back may apply Socratic questioning with the help of the group to identify and challenge cognitive distortions. Participants will be asked to complete live worksheets through the web-based platform, and they will be asked to complete weekly home exercises using downloadable materials. Therapists will troubleshoot and track the prior week’s home practice at the beginning of each subsequent session.

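### CBSM is delivered in therapy groups and the control individually, but the secondary-outcome tests treat all men as independent; if outcomes correlate within groups, the stated 5% error is not held

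*Protocol article*

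**What the plan says.** **Delivery.** The Study Design section of the protocol article assigns men 1:1 to "10 individual sessions of video-adapted health promotion (HP) content (educational control) or 10 group-based sessions of the SmartManage intervention". The planned size is 50: "The pilot study will enroll 50 SMM who are HIV positive". The section describing the adapted CBSM adds: "Intervention groups consist of 4 to 6 participants led by a trained therapist". The section on the HP educational control has each control man log on to the platform and view one new video a week.

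**Analysis.** The Data Analytic Plan (Aim 2) sets the error level for intervals and tests alike: "Type 1 error will be set to 5% (α=.05) for calculating CIs and performing hypothesis testing". For stress, disease-related distress and HRQoL it names paired *t* tests for change within each arm and independent samples *t* "tests to analyze potential differences in outcomes between the study groups (SmartManage intervention vs educational control"). Repeated measures ANOVA then serves "to explore whether effects remain when accounting for sociodemographic, medical, and psychosocial covariates". The listed covariates all describe the participant. Neither therapy group nor therapist is named as a factor. The room left for changing the plan covers distributions, missing data and multiple comparisons.

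**The concern.** This is a partially nested design: men in one arm share a therapy group and its leader for ten weeks, and men in the other arm share nothing. Group interaction is part of the CBSM treatment, since members help one another to challenge distorted thoughts and to practise skills. Their outcomes may therefore be correlated after treatment. The named tests assume that they are not.

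Repeated measures ANOVA does not remove the problem. It allows for correlation between one man's two assessments, not between men in the same group. With two occasions and no covariates, its arm-by-time test is the independent *t* test on change scores.

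What is at stake is the precision of the secondary estimates. Ignoring the grouping leaves the estimated mean difference unbiased, but with a positive within-group correlation its standard error is too small. The interval then covers less often than stated, and a nominally significant result is weaker evidence than it looks. The paired test within the CBSM arm is hit harder, because no ungrouped arm dilutes the effect.

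**Working it through.** **Inputs from the document.** 50 men allocated 1:1, so 25 per arm; CBSM groups of 4 to 6; controls individual; α = 0.05. The plan states two-sided testing for the feasibility and acceptability comparisons ("independent samples 2-tailed *t* test and ANOVA"); the same is assumed here for the intended effects.

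**Number of groups.** 25/6 = 4.2, so at least five groups. 25/4 = 6.25, so at most six. Two layouts were checked: five groups of 5, and six groups of 4, 4, 4, 4, 4 and 5.

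**Assumed.** The ICC (ρ) within CBSM groups of the score being analysed, from 0 to 0.20. Total variance is equal in both arms.

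**Formulas.**
- Design effect in the CBSM arm: DEFF = 1 + (m − 1)ρ, with m = Σmᵢ²/Σmᵢ. For five groups of 5, m = 5. For the six-group layout, m = (5 × 16 + 25)/25 = 4.2.
- True over naive standard error, between arms: √[(DEFF/25 + 1/25)/(2/25)] = √[(DEFF + 1)/2]. Within the CBSM arm: √DEFF.
- Real type 1 error: 2[1 − Φ(1.96/ratio)].

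**Worked example, five groups of 5 at ρ = 0.10.** DEFF = 1 + 4 × 0.10 = 1.40. The between-arm ratio is √1.20 = 1.095; 1.96/1.095 = 1.79, giving 7.4%. The within-arm ratio is √1.40 = 1.183; 1.96/1.183 = 1.66, giving 9.8%.

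**Results.** Each error cell shows the formula result, then a simulation of 200,000 null data sets.

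| Layout | ICC | DEFF | SE ratio between arms | Between-arm *t* test, % | Paired test within CBSM, % |
|---|---|---|---|---|---|
| Five groups of 5 | 0 | 1.00 | 1.000 | 5.0 / 5.0 | 5.0 / 5.1 |
| | 0.01 | 1.04 | 1.010 | 5.2 / 5.2 | 5.5 / 5.5 |
| | 0.05 | 1.20 | 1.049 | 6.2 / 6.1 | 7.4 / 7.3 |
| | 0.10 | 1.40 | 1.095 | 7.4 / 7.4 | 9.8 / 9.7 |
| | 0.20 | 1.80 | 1.183 | 9.8 / 9.9 | 14.4 / 14.5 |
| Six groups (4,4,4,4,4,5) | 0.01 | 1.032 | 1.008 | 5.2 / 5.1 | 5.4 / 5.3 |
| | 0.05 | 1.16 | 1.039 | 5.9 / 6.0 | 6.9 / 6.9 |
| | 0.10 | 1.32 | 1.077 | 6.9 / 6.9 | 8.8 / 8.8 |
| | 0.20 | 1.64 | 1.149 | 8.8 / 8.8 | 12.6 / 12.5 |

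The first row reproduces the plan's own figure: 5% is right if men in a group are uncorrelated.

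**After dropout.** At the 85% retention target (0.85 × 25 ≈ 21 per arm; groups of 4, 4, 4, 4 and 5), the between-arm figures are about 6%, 7% and 9% at ICC 0.05, 0.10 and 0.20. Dropout makes the groups smaller and eases the problem slightly.

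**The case against.** **It depends on an ICC that nobody has stated.** This stands. A reader might infer that type 1 error will certainly exceed 5%. The document does not support that: at ICC 0 the 5% holds, and at 0.01 the inflation is negligible. It gives no reason to assume zero either.

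**The affected tests are secondary.** This also stands. The section on intended effects says that the study does not set out to test efficacy. The feasibility criteria (70% of starters attending at least 70% of sessions, 85% retention) and the 30% agreement criterion for acceptability are fixed proportions with no test attached. A reader might infer that the feasibility decision is compromised; it is not. Nor does the article say that the next trial will be sized from these estimates. It says only that the lessons may inform larger trials.

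**Harsher layouts and structures.** One might picture the 25 men in four large groups, but one group would then need seven members, above the stated maximum of six. One might also assume a separate therapist for each group. The number of therapists is not given. If one therapist leads several groups, that could add correlation across groups.

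**A statistical analysis plan could settle it.** This does not answer the point. The article does not leave the method open: it names tests that assume independence and sets their error level, while its own delivery format puts that assumption in doubt.

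**The controls may meet in groups too.** The section on content and format describes the weekly live meeting just after text about both conditions. However, the Study Design and HP control sections make clear that the control is individual.

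**Conclusion.** The point holds in conditional form, for the secondary intended-effects analyses. The design clusters men in the CBSM arm only, and the planned tests ignore it. If the ICC is between 0.05 and 0.20, the between-arm *t* test runs at about 6% to 10% with five groups and 6% to 9% with six. The paired test within the CBSM arm runs at about 7% to 15%. Nominal 95% intervals for the arm difference would then cover about 90% to 94%. At an ICC near 0.01 nothing of practical importance changes.

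These figures rest on an assumed ICC, equal total variance in the two arms and full enrolment of 25 per arm. The missing group term is certain; the size of the inflation is not. The change should be made because it is cheap and because the plan still promises tests and intervals at 5%.

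**What to change.** - Record therapy-group and therapist identity for every CBSM participant.
- Replace the between-arm *t* test and repeated measures ANOVA with a partially nested mixed model: a random group effect in the CBSM arm only, each control as his own cluster, and Satterthwaite or Kenward-Roger degrees of freedom. Keep the group term whatever its estimated size.
- Test change within the CBSM arm with the group effect included.
- If confidence intervals are given for CBSM attendance, adjust them for group, since members share a meeting time and a leader.
- If an ICC is reported, give its confidence interval and do not rely on it for planning. With a true ICC of 0.05 and five groups of 5, the estimate has a 95% sampling range of about −0.21 to 0.41 and is zero or negative in about 46% of simulated trials.

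The cost is one or two recorded variables, a changed model statement and somewhat wider intervals, because there are only five or six groups. No extra participants or visits are needed.

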Participants will meet the following inclusion criteria: (1) ≥18 years of age; (2) fluent in English; (3) diagnosed with at least 1 form of nonmetastatic solid tumor or blood cancer; (4) ≥30 days after the completion of active primary treatment (eg, surgery, radiation, and chemotherapy); (5) self-identify as a sexual minority, cisgender man (ie, self-identify as something other than heterosexual or straight; assigned male at birth and identify as male); (6) self-report having been diagnosed with HIV; and (7) have reliable access to a device with internet access. Adjuvant therapies such as hormone treatment for prostate cancer are not considered exclusionary. Participants will be excluded if they (1) have one of the following exclusionary cancer types: nonmelanoma skin cancer only, brain cancer, eye cancer, or remote history of pediatric cancer only without a history of cancer as an adult; (2) have a history of metastatic cancer of any type; (3) are currently undergoing primary treatment for their cancer; (4) have had inpatient treatment for serious mental illness in the past 12 months, overt signs of serious mental illness, or moderate or higher risk of suicidality at the time of screening; (5) appear actively intoxicated or otherwise unable to provide full informed consent; or (6) have any medical conditions resulting in a predicted life expectancy of <12 months per participant self-report. The intention behind the specificity of these inclusion and exclusion criteria is to minimize the enrollment of participants whose illness is likely to significantly interfere with their ability to engage with the study material (eg, eye cancer) or complete study participation (eg, metastatic illness with a life expectancy of <12 months). The research team felt that this was necessary given the small sample size of this study; however, we also recognize that some patients excluded from this study could benefit from the intervention. We intended to expand inclusion criteria in larger subsequent studies to allow broader medical inclusion and applicability to participants of other genders and sexual orientations.

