### Data Collection

#### Sociodemographic and Medical History or Status

Participants in both phases will report sociodemographic data including age, race, ethnicity, sex assigned at birth, gender identity, education, income, and household makeup. Participants in both phases will also self-report information about their cancer, HIV, and relevant health behaviors. This includes diagnosis dates, past and current treatments, and medication or treatment adherence. Cancer-specific questions include the type of cancer and whether their cancer has metastasized. HIV-specific questions relate to the frequency of contact with HIV care providers, current viral load, and CD4 count. We will also ask about any barriers they face regarding access to HIV care, such as difficulty obtaining medications or feeling stigmatized by health care providers. Participants in phase 2 will be reassessed after the intervention for information that may change (eg, HIV viral load and cancer prognosis). Table 1 lists all study measures collected.

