#### Primary Outcomes: Feasibility and Acceptability

As the main purpose of the SmartManage study is intervention development, quantitative primary outcomes are focused on participant engagement in phase 2 (pilot testing). For the adapted SmartManage CBSM for HIV and cancer intervention to be considered feasible, 70% of the participants who begin the intervention will attend at least 70% of all intervention sessions, and 85% of the enrolled participants will be retained throughout the study. These proportions are based on previously successful CBSM trials in other populations [21-23]. We will also examine cost indicators of implementation feasibility by documenting personnel time, space requirements (eg, for intervention delivery and study administration), and supply costs, including the maintenance and management of the SmartManage website.

We will evaluate intervention acceptability in two ways: (1) the proportion of eligible SMM in phase 2 who agree to participate versus decline (≥30%) and (2) via 2 exit surveys administered after participants have completed the SmartManage intervention. One such survey is the commonly used Usefulness, Satisfaction, and Ease of Use (USE) questionnaire [24], which assesses participants’ impressions of the intervention’s usefulness, ease of use, ease of learning, as well as overall satisfaction with the intervention. We also created an intervention-specific measure to evaluate participants’ views on SmartManage elements that are not assessed in the USE questionnaire. These include perceptions of relevance to health needs, how helpful the program is for SMM with HIV and cancer, and the willingness to recommend the program to similar peers. Both intervention acceptability measures ask participants to rate items on a 7-point Likert scale ranging from *strongly agree* to *strongly disagree*. Both measures also include qualitative questions with open text response fields allowing participants to share thoughts on what they found most and least helpful, what important areas were not addressed sufficiently, and recommendations to improve the intervention.

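### The check of whether between-arm effects survive adjustment uses an open covariate set (about 20 varying items for about 43 completers, read literally), so an effect could seem to vanish through lost precision alone

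*Protocol article*

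**What the plan says.** Under Aim 2 of the Data Analytic Plan, the between-arm analysis has two steps: independent-samples t tests, then repeated measures ANOVA "to explore whether effects remain when accounting for sociodemographic, medical, and psychosocial covariates". The sentence on within-group change has the same two-step form and identifies its covariates as follows: "accounting for the sociodemographic, medical, and psychosocial covariates described earlier". Neither sentence gives a number, a list or a rule for choosing.

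The variables are described in three earlier places:

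- **Sociodemographic and Medical History or Status** lists "age, race, ethnicity, sex assigned at birth, gender identity, education, income, and household makeup", followed by cancer, HIV and treatment items.
- **Other Psychosocial Factors** adds discrimination and acculturation, both introduced as possible moderators.
- **Nature of Illness** adds two COVID-19 measures.

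Under Participants, eligibility requires men who are "assigned male at birth and identify as male" and excludes any history of metastatic cancer.

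On size, "The pilot study will enroll 50 SMM who are HIV positive", allocated 1:1. The feasibility target is that "85% of the enrolled participants will be retained throughout the study".

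**The concern.** In a randomized comparison, baseline covariates are not systematic confounders. Adjusting for them serves precision, and asking whether an effect survives adjustment is a check borrowed from observational work. With many covariates and few participants, the answer can turn on lost degrees of freedom and chance imbalance between arms, even when the expected treatment difference is unchanged.

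The between-arm comparison is the stated secondary aim, and the Discussion says the lessons learned may inform larger randomized trials. For that use, the estimate and its interval matter most. A needlessly wide interval, or a report that an effect did not hold up after adjustment, would mislead whoever plans the next study.

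Two features suggest that the described set was not screened for modelling. Sex assigned at birth, gender identity and metastasis cannot vary at entry. Medication adherence appears both as a descriptor and as an intended effect. In addition, items that may change are reassessed after the intervention, and the analysis paragraph does not restrict adjustment to T1 values.

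**Working it through.** The article gives no power or sample-size calculation for the effect analyses, so there is no figure to reproduce.

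**Completers.** 50 × 0.85 = 42.5, about 43 (22 and 21 by arm). This takes the retention target as the outcome.

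**Covariates if every described item is entered.**
- Sociodemographic: 8.
- Medical: about 11. These are two diagnosis dates, past treatment, current treatment and adherence (5); cancer type and metastasis (2); frequency of HIV care contact, viral load, CD4 count and barriers to care (4).
- Psychosocial: about 4 (discrimination, acculturation, two COVID-19 measures).
- Total: 8 + 11 + 4 = 23. Less the 3 that are constant by eligibility, about 20 vary, before dummy coding of race, cancer type and similar items.

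**Precision when the covariates are unrelated to the outcome.** For n participants and p covariates:
- Residual df = n − 2 − p = 43 − 2 − 20 = 21, against 41 unadjusted.
- Expected variance inflation from chance imbalance = (n − 3)/(n − 3 − p) = 40/20 = 2.0, so the SE is multiplied by √2 = 1.414.
- CI-width ratio = 1.414 × t(21)/t(41) = 1.414 × 2.080/2.020 = 1.456.
- Break-even joint R² = 1 − 1/1.456² = 0.53. Above this, adjusting for all 20 narrows the interval.
- The same formulas give a ratio of 1.166 and break-even of 0.27 for 10 covariates, and 1.074 and 0.13 for 5.

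**Simulation.** There were 5,000 trials per cell, with 22 against 21 participants, two-sided α = 0.05 and independent covariates. The assumed effect was d = 0.875, which gives the unadjusted t test 80% power. Each participant contributes one outcome or change score.

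| Covariates | Joint R² | Adjusted power | Significant unadjusted results lost | Mean CI-width ratio |
|---|---|---|---|---|
| 20 | 0 | 51% | 39% | 1.44 |
| 20 | 0.2 | 59% | 30% | 1.29 |
| 20 | 0.4 | 71% | 22% | 1.12 |
| 20 | 0.5 | 78% | 17% | 1.02 |
| 20 | 0.6 | 87% | 9% | 0.92 |
| 10 | 0 | 68% | 18% | 1.16 |
| 10 | 0.2 | 78% | 12% | 1.04 |
| 5 | 0 | 74% | 10% | 1.07 |
| 5 | 0.2 | 83% | 7% | 0.96 |
| 5 | 0.4 | 92% | 3% | 0.84 |

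Unadjusted power was 79–81% in every row. The mean adjusted estimate was 0.87 to 0.88 throughout, so the losses come from imprecision and not from a shrinking effect.

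**Full retention.** With all 50 analysed and 20 covariates: inflation 47/27 = 1.74, SE ratio 1.319, CI-width ratio 1.319 × 2.048/2.011 = 1.34. The cost is smaller but still present.

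**The case against.** The strongest objection is that the count is inferred. The article nowhere says that all items enter one model. Much of the list sits under Data Collection, discrimination and acculturation are introduced as moderators, and the pointer to covariates already described is in the within-group sentence, not the between-arm one. A condensed article may leave the choice of covariates to an analysis plan. This stands: about 20 is what a literal reading gives, not what the plan states. It does not dispose of the point, because the article goes beyond leaving out a list. It states a rule, that effects are to be checked for survival after adjustment, and that rule is unsound after randomization whatever the count.

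A reader might infer three stronger things that the documents do not support:

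- **That the constant items cause the loss of precision.** They do not. They are collinear with the intercept, drop out and use no degrees of freedom.
- **That real effects will look explained away.** Even with 20 covariates and R² = 0, about 61% of significant results stay significant, and with strongly prognostic covariates adjustment helps.
- **That the plan makes significance after adjustment the between-arm criterion.** Only the within-group sentence does so. The between-arm step is described as exploration, so the figures for lost significance show what could follow if it is read in the same way.

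Other mitigating facts also stand. The primary outcomes are feasibility and acceptability, the article disclaims any test of efficacy, and the unadjusted t test remains in the plan. At 85% retention, 15% of participants would lack T2 data, so multiple imputation might be used under the plan's 10% rule and the analysis would not necessarily be confined to 43 completers.

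**Conclusion.** The point holds in a limited form. Aim 2 poses the wrong question for a randomized comparison and attaches it to a covariate set that 43 completers may not support. If every varying item were entered and were weakly prognostic, the interval could be up to about 46% wider, power could drop from 80% to about 50–60%, and about 30–39% of significant unadjusted effects could lose significance without any change in the average estimate.

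These sizes rest on assumptions that the article does not supply: about 20 covariates, retention at target, d = 0.875, independent covariates and a joint R² of 0 to 0.2. They also assume that covariates act on the change score, as when each is crossed with time; covariates entered only as main effects would leave the group-by-time contrast largely untouched. With 10 covariates the cost is modest, and above a joint R² of about 0.53 even 20 would gain precision. This is a worthwhile correction to a secondary analysis and no threat to the primary outcomes.

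**What to change.** In the last paragraph of Aim 2, replace the open covariate set with the outcome's own T1 score plus a few prognostic covariates, for example two to five, measured at T1 and named before outcome data are seen. Leave out sex assigned at birth, gender identity and metastasis, which are constant by eligibility. Report the adjusted between-arm difference with its 95% CI as the main effect estimate; the unadjusted difference may be shown beside it. Delete the reading of whether effects survive adjustment.

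The cost is about two sentences and no new data. The downside is that the remaining covariates are described by arm and not adjusted for. The simulation suggests this is a small price: with five covariates, power is 74% at R² = 0, 83% at 0.2 and 92% at 0.4, against about 80% unadjusted.
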